## 12. SAFETY

### 10.1. Safety instructions

- a. The safety and tolerability of the treatment will be evaluated based on the registration of adverse events (AEs) and the classification of laboratory evaluations and vital signs. A severity rating scale, based on the local symptomatology rating scales of all symptoms, physical examination findings, and test results will be used (see Appendix B and C).
- b. All laboratory abnormalities (see Appendix C)

### 10.2 Definitions of an adverse event (AE)

An adverse event is any undesired medical occurrence in a patient or clinical trial participant who is administered a pharmaceutical product; such an occurrence need not necessarily be causally related to the treatment.

*A priori*, the safety outcomes specified in the protocol will not be considered as AEs unless, due to the evolution, severity or any other characteristics of these events that exceed the established safety limits, the investigator, according to their clinical judgment.

In this study, adverse events, such as itching, skin redness, changes in skin pigmentation, bruising, scarring, peeling, skin depression, and textural and thickness changes, will be described in both arms, during the follow-up.

[figure not shown][figure not shown]

## **11. MANAGEMENT OF TEMPORARY OR DEFINITE DISCONTINUATION OF TREATMENT AND STUDY DISCONTINUATION**

Any discontinuation of the experimental product must be fully recorded on the CRF. In any case, the patient must remain in the study for the period of 3 days of hospitalization and return if there is any discomfort or worsening of the clinical condition.

### **11.1 Permanent discontinuation of treatment**

c. Permanent discontinuation of treatment means any discontinuation associated with the definitive decision by the investigator or the patient not to re-expose the patient to the research product.

#### **11.1.1 List of criteria for permanent discontinuation of treatment**

Patients can withdraw from the treatment of their own free will, at any time and regardless of reason, or this can also be decided by the investigator. Every effort should be made to document the reasons for discontinuing treatment in the CRF.

The objective criteria for discontinuing the study treatment and adopting a safe treatment are as follows:

- Revocation of the informed consent form: The patient or his parents or guardians may withdraw from treatment with the Experimental Product if they so decide, at any time and regardless of justification, or this may be by decision of the Investigator,
- Onset of infection.
- Manifestation of an adverse event that justifies discontinuation of treatment.

[figure not shown][figure not shown]

### **11.2 Procedure for withdrawing patients from the study**

Patients may withdraw from the study, before its end, if they so wish, at any time and regardless of justification, or this may occur by decision of the investigator.

Enrolled patients will be withdrawn from the study for the following reasons:

1. Revocation of the informed consent form
2. Development of any serious adverse event requiring study interruption
3. Inability to comply with the study design and procedures
4. Diagnosis of a serious chronic illness that requires frequent medical care.

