In these areas, among the medically important snakes involved in the envenomations, *Bothrops jararacussu*, popularly known as « jararacuçu », is found in Brazil, Bolivia, Paraguay and northeastern Argentina. In Brazil, it is also the snake with the highest venom production and injection capacity (400 mg)(10), and one of the most important venomous vipers of the viperidae family in Latin America, reaching a maximum length of 220 cm(11).

The venom of species belonging to the genus *Bothrops* has a predominantly proteolytic, coagulant, hemorrhagic, inflammatory, edematogenic and myotoxic effect(12). The clinical signs exhibited by *Bothrops* envenomations are due to the various components that are isolated from these secretions, such as the hemorrhagic factor, i.e., proteases that act in blood coagulation causing coagulation disorders, proteolytic enzymes and myotoxins(13). Among the main enzymatic proteins with myotoxic activity found in snake venoms are proteolytic enzymes and phospholipases(12)(14).

*Bothrops* venom can cause systemic effects, such as bleeding in pre-existing wounds, cardiovascular and renal alterations, gingival bleeding, epistaxis, hematemesis, hematuria, uterine bleeding (pregnant women), vomiting, nausea, sweating, arterial hypotension and shock(15). In envenomations by these species, the

victim will commonly have evident local effects, which may vary in intensity, and which are represented by pain and edema that sets in early and evolves progressively. Ecchymosis, bleeding, ganglionic enlargement, blisters and necrosis may also appear, and it is possible to have functional or even anatomical loss of the affected limb as sequelae(16).

Among the local reactions, cell necrosis can result in loss of tissue function in the affected limb(17). Thus, the myonecrosis caused by *Bothrops* venoms may have an indirect action as a result of the degradation of blood, vessels and ischemia caused by metalloproteinase or by the direct effect of the homologous myotoxic phospholipases A2 (PLA2s) on the plasmatic membrane of skeletal muscle cells(18).

Metalloproteinases, on the other hand, have a hemorrhagic action in *Bothrops* venoms, causing hemorrhage followed by myonecrosis and arterial necrosis, and enhance myotoxicity as a result of reduced muscle perfusion and circulatory deprivation, which also affects muscle regeneration(19).

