#### **7.5. Criteria for study interruption**

If the study does not show benefits, for example, the control group shows improvement and the low-power laser groups do not. The presence of marked myonecrosis will also indicate the need for the discontinuation of the study.

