## 9.2 Secondary

### Prevention of myonecrosis

Efficacy should be evaluated according to the results of creatine kinase (CK) in the follow-up period (see Appendix A).

- The increase in CK indicates myonecrosis, which should be investigated from the first moment with the patient and after 24 h, 48 h and 72 h. When the patient returns on the 7th day, CK testing will also be performed and evaluated in the two arms of the clinical trial.

Other secondary parameters include:

- Proportion of any adverse events, such as itching, skin redness, changes in skin pigmentation, bruising, scarring, peeling, skin depression, and textural and thickness changes.

[figure not shown][figure not shown]

---

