### **11.3 Consequence**

Patients who are withdrawn from the study cannot be re-enrolled. Your inclusion number and treatment number must not be used again. In specific situations to be discussed between the investigator and sponsor, patients who have not yet been randomized may be re-included in the study.

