#### 12.1.1 Inclusion visit: D1, D2, D3

On the first day (**D1**), the patient is seen and randomized to one of the 2 groups.

- In Arm 1, patients will be part of the control, where after completing the clinical form, the signs and symptoms and collection of laboratory tests, they will receive the application of the low-power 4J laser at the site of the snakebite, but turned off.

- In Arm 2, patients, after completing the clinical form, the signs and symptoms and collection of laboratory tests, will receive the application of a low-power 4J laser at the site of the snakebite 30 minutes after the infusion of Antivenom (AV).

On the second day (**D2**), 24 hours after the first application, patients were randomized:

[figure not shown][figure not shown]

---

- In Arm 1, the control patients, after verifying the signs, symptoms and collection of laboratory tests, will receive the application of a low-power 4J laser at the site of the snakebite, but turned off.

- In Arm 2, patients will receive after the signs, symptoms and collection of laboratory tests, will receive the application of low- power laser in 4J at the site of the bite.

On the third day (D3), 48 hours after the first application, patients were randomized:

- In Arm 1, the control patients, after verifying the signs, symptoms and collection of laboratory tests, will receive the application of a low-power 4J laser at the site of the snakebite, but turned off.

- In Arm 2, patients, after verifying the signs, symptoms and collection of laboratory tests, will receive the application of a low-power 4J laser at the site of the bite.

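### Section 11.2 requires randomised patients to be withdrawn from the study for inability to comply, which conflicts with section 11 when the missed procedure is the laser or sham session

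*Protocol*

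**What the plan says.** Three parts of the Protocol bear on this.

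- **Section 11.2** is mandatory in tone: "Enrolled patients will be withdrawn from the study for the following reasons". The third of four reasons is "Inability to comply with the study design and procedures". The others are revoked consent, a serious adverse event requiring study interruption, and a newly diagnosed serious chronic illness.
- **Section 11.3** bars re-enrolment of withdrawn patients and retires their treatment number. Its only exception is that, by agreement between investigator and sponsor, "patients who have not yet been randomized may be re-included in the study".
- **Section 11** opens with discontinuation of the experimental product, has it recorded on the CRF, and adds: "In any case, the patient must remain in the study for the period of 3 days of hospitalization".

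On timing, section 12.1.1 has day 1 as the day on which "the patient is seen and randomized to one of the 2 groups". Laser or sham is applied on days 1, 2 and 3. Section 13.2 compares means by t-test at 48 hours after admission. Section 9.2 schedules CK at 24, 48 and 72 hours, and for the day-7 return it says "CK testing will also be performed and evaluated in the two arms of the clinical trial".

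**The concern.** A randomised patient may be unable to take the remaining laser or sham sessions yet still be in a hospital bed, consenting and measurable. Section 11 keeps that patient in the study. Section 11.2 takes the patient out. A site that follows 11.2 stops collecting readings it could have taken, and no analysis plan written afterwards can recover them.

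Two things are at stake. One is precision, since each such loss shrinks an arm of 30. The other is the randomised comparison, which is distorted if those withdrawn differ between arms in a way related to outcome.

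**Working it through.** **1. Does 11.2 reach randomised patients?** It says enrolled, not randomised, so this has to be inferred. Section 11.3 gives withdrawn patients a treatment number and allows re-inclusion only for those not yet randomised, so it supposes that some withdrawn patients have been randomised. Randomisation is on day 1 (12.1.1), so non-compliance with the sessions normally arises after it. The inference is firm.

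**2. Where do the two rules collide?** Section 11 governs patients who discontinue the product. Section 11.2 governs patients leaving the study. They overlap when the procedure the patient cannot comply with is the laser or sham session. For that patient one rule says stay and the other says leave.

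**3. What would be lost?** That depends on when the patient is withdrawn:
- after day 1: the 24-hour and 48-hour readings and everything later;
- after day 2: the 48-hour readings and everything later;
- on day 3: the pre-application signs and bloods are already taken (12.1.1), but thermography after the application (8.1) and the 72-hour and day-7 CK (9.2) are still to come.

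**4. Size: precision.** The Protocol gives no power, SD, effect size or dropout rate, so it has no figure to reproduce. Inputs: 30 per arm (Synopsis) and significance level 0.05 (13.2). Assumed: a two-sided test, 80% power, and 3 patients lost per arm. Solving the noncentral-t power equation for the standardised difference d, with noncentrality d × √(n/2) and 2n − 2 degrees of freedom:
- n = 30 per arm: d = 0.736 SD
- n = 27 per arm: d = 0.777 SD

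Equivalently, power for a true difference of 0.736 SD falls from 80% to about 76%.

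**5. Size: bias.** Assume k laser patients and no controls are withdrawn, and that their 48-hour values are 1 SD worse than those of the patients who remain. The laser mean then looks better by k × 1/30 SD:
- k = 1: 0.033 SD
- k = 2: 0.067 SD
- k = 3: 0.100 SD

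Trials were simulated with no true laser effect, the same mix of patients in both arms, and a t-test of 30 − k against 30. The share falsely favouring the laser (nominal 2.5%) was:
- k = 1: about 3.2%
- k = 2: about 4%
- k = 3: about 5%

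With the same k withdrawn from both arms, the share stays at about 2.4% to 2.6%, which is nominal.

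**The case against.** The strongest reply is that the conflict is narrow. Section 11 speaks of stopping the product and 11.2 of leaving the study, so a reader might infer a flat contradiction for every non-compliant patient. The documents do not support that. Someone who cannot be assessed at all yields no reading under either rule. This part stands and limits the point to missed laser or sham sessions.

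Second, the exits most plausibly related to outcome are handled elsewhere. Rising CK, worsening inflammatory signs and infection lead to stopping treatment under 7.4 and 11.1.1, not to leaving the study, so section 11 keeps those patients. Reason 3 is a residual category in a short inpatient trial where staff apply the device. This also stands.

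Third, the bias scenario is one-sided by construction. Controls undergo the same procedure with the laser off, under blinding, and the Protocol gives no reason to expect non-compliance in one arm only. The scenario shows what would be needed for harm; it is not a forecast.

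Fourth, removing reason 3 leaves 11.2's general permission for the investigator to withdraw a patient, and its serious-adverse-event reason. That is true, but neither compels the removal of a measurable inpatient merely for adherence, which is what reason 3 does.

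A reader might also infer a companion fault in section 7.5, "The presence of marked myonecrosis will also indicate the need for the discontinuation of the study": that one case in either arm, including a sham patient with the venom effect described in 4.1 ("causing hemorrhage followed by myonecrosis and arterial necrosis"), stops the trial. The text does not say so. It names no arm and no count, follows a sentence comparing control with laser, and leaves room for judgement. Replacing it with an excess in the laser arm would need a threshold and someone who sees counts by arm, so that is a trade-off and not a correction.

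**Conclusion.** The point holds in its narrow form. Section 11.2, read with 11.3 and 12.1.1, requires withdrawal of randomised patients for inability to comply. Where that means the laser or sham sessions, it contradicts section 11 and discards obtainable readings before the 48-hour comparison. An analysis plan can define analysis sets but cannot restore data that were never collected, so the remedy belongs in the Protocol.

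The likely size is small. Three unbiased losses per arm move the detectable difference by about 0.04 SD (0.777 − 0.736). The 3% to 5% false-favourable rates rest wholly on assumed one-sided losses of patients 1 SD worse, and the Protocol gives no rate of non-compliance. The change is worth making because it costs almost nothing, not because serious bias has been shown. Section 7.5 is not part of this conclusion.

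**What to change.** Delete reason 3 from section 11.2, or limit it to patients not yet randomised. Add that a randomised patient who cannot complete the sessions:
- stops laser or sham only;
- keeps every scheduled assessment: 24 hours, 48 hours, and the 72-hour and day-7 CK of section 9.2;
- is analysed in the arm to which he or she was randomised.

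A patient who refuses assessments can still revoke consent, which remains a reason for withdrawal.

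The cost is a change of wording. No visit is added: the 24-hour and 48-hour readings fall within the hospital stay, and the 72-hour and day-7 CK are already scheduled.

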### **11.3 Consequence**

Patients who are withdrawn from the study cannot be re-enrolled. Your inclusion number and treatment number must not be used again. In specific situations to be discussed between the investigator and sponsor, patients who have not yet been randomized may be re-included in the study.

## 12 STUDY PROCEDURES

### 12.1 Scheme of visits

[figure not shown]

Figure 1 - Recruitment Flowchart

#### 12.1.1 Inclusion visit: D1, D2, D3

On the first day (**D1**), the patient is seen and randomized to one of the 2 groups.

- In Arm 1, patients will be part of the control, where after completing the clinical form, the signs and symptoms and collection of laboratory tests, they will receive the application of the low-power 4J laser at the site of the snakebite, but turned off.

- In Arm 2, patients, after completing the clinical form, the signs and symptoms and collection of laboratory tests, will receive the application of a low-power 4J laser at the site of the snakebite 30 minutes after the infusion of Antivenom (AV).

On the second day (**D2**), 24 hours after the first application, patients were randomized:

[figure not shown][figure not shown]

---

- In Arm 1, the control patients, after verifying the signs, symptoms and collection of laboratory tests, will receive the application of a low-power 4J laser at the site of the snakebite, but turned off.

- In Arm 2, patients will receive after the signs, symptoms and collection of laboratory tests, will receive the application of low- power laser in 4J at the site of the bite.

On the third day (D3), 48 hours after the first application, patients were randomized:

- In Arm 1, the control patients, after verifying the signs, symptoms and collection of laboratory tests, will receive the application of a low-power 4J laser at the site of the snakebite, but turned off.

- In Arm 2, patients, after verifying the signs, symptoms and collection of laboratory tests, will receive the application of a low-power 4J laser at the site of the bite.

## 12.2 Definition of source data

All data and information requested in the clinical record (CRF) will be collected in a patient file (iDoctor medical record) after interviewing the patient, including vital and clinical signs, laboratory tests, concomitant illnesses and any possible concomitant medications

Dates of visits and demographic data will be recorded on the CRF along with printed laboratory test results and will be filed with the patient's medical file. Treatments will be recorded in a file or spreadsheet created for this purpose.

---

## 13. STATISTICAL CONSIDERATIONS

### 13.1 Preliminary analysis

After the admission of the first 30 patients, this study foresees a preliminary analysis for the validation of the application of the low-power laser in arms 1 and 2, to eventually recalculate the number of patients to be included or not.

### 13.2 Statistical and analytical plans

Feasibility outcomes were analyzed using descriptive statistics as proportions. Trial outcomes were reported as means and standard deviations. We report the outcomes using means and standard deviations, and we conducted inferential analysis on our data in order to report the differences between the two groups. Mean values of creatine phosphokinase activity, pain intensity, circumference measurement ratio, extent of edema, difference between the bite-site temperature and that of the contralateral limb, and disability assessments, were compared using the t-test for independent samples, at 48 hours after admission. A Kaplan-Meier survival analysis with a log-rank test was performed to detect differences in the time elapsed from admission to the day of reduction by 50% in creatine phosphokinase activity, pain intensity, circumference measurement ratio, extent of edema and difference between the bite-site temperature and that of the contralateral limb between the intervention and comparator groups, at two points - on 24 and on 48 hours after admission. The comparison of the frequency of use of analgesics, secondary infections and necrosis in a follow-up of 48 hours, between the intervention and comparator groups, was made using the Chi-square or Fisher's exact test; odds ratios with 95% confidence intervals were obtained. The Kruskal-Wallis rank sum test was used to compare the disability scores between groups, for each domain score and for the summary score. Statistical analyses were performed in the R software in the IDE Rstudio environment (version 4.1.2), and the significance level of the tests was 0.05.

[figure not shown][figure not shown]

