|                                                  |                                                                                                                                                                                                                                                                                                                                                                                                                                                                                                                                                                                                                                                                                                                                                                                                |
|--------------------------------------------------|------------------------------------------------------------------------------------------------------------------------------------------------------------------------------------------------------------------------------------------------------------------------------------------------------------------------------------------------------------------------------------------------------------------------------------------------------------------------------------------------------------------------------------------------------------------------------------------------------------------------------------------------------------------------------------------------------------------------------------------------------------------------------------------------|
| 
Expected total number of patients:
 | 
d) Patient is immunocompromised;
e) Patient is on a course of anti-inflammatories or antibiotics;
f) Patient has diabetes mellitus (DM).
 
60 patients, 30 in the treatment group and 30 in the control group, stratified as follows:
 
Arm 1) Considered the control group, this arm will receive conventional treatment from the date of admission to the hospital and will also receive the protocol with the laser turned off, therefore without any effect.
 
Arm 2) This arm will receive the laser treatment within 30 minutes after the infusion of antivenom serum at a dose of 4j/cm^2.
                                                                                                                                                      |

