| 
EVALUATION SCHEME
          | 
Patients will be evaluated with the same parameters irrespective of the group to which they were allocated at the time of admission, and at 24 and 48 hours in relation to clinical and laboratory aspects.
                                                                                                                                                                                                                                                                                                                                                                                                                                                                                                                                                                                                                                                                                                                                                                                                                 |
| 
STATISTICAL CONSIDERATIONS
 | 
Number of patients:
 
A priori, 60 patients in order to evaluate the effectiveness and safety of low-intensity laser in sites of snakebites involving the genus Bothrops.
 
Statistical generalities:
 
This study foresees the performance of an interim analysis when the groups reach half of their recruitment, i.e., 15 patients in each group. This analysis will be able to identify variations related to the primary outcome and will indicate the need for continuity, restructuring, or finalization of the study. Quantitative variables will be calculated for frequency and proportions, with the calculation of means.
 
Feasibility outcomes were analyzed using descriptive statistics as proportions. Trial outcomes were reported as means and standard deviations. We report the outcomes using means and standard deviations, and we conducted inferential analysis on our data in order to report the differences between the two groups. Mean values
 |

[figure not shown][figure not shown]

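### The 48-hour t-tests leave out admission values held for five of the six measures: a valid test, but an inefficient one with 30 patients per arm

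*Protocol*

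**What the plan says.** Section 13.2, repeated in the Synopsis under statistical considerations, lists the variables as "Mean values of creatine phosphokinase activity, pain intensity, circumference measurement ratio, extent of edema", followed by the bite-site-to-contralateral temperature difference and disability. It states that they "were compared using the t-test for independent samples, at 48 hours after admission". No covariate, change score or transformation is named. The summary is equally plain: "Trial outcomes were reported as means and standard deviations". The level is given as "the significance level of the tests was 0.05", without saying whether tests are one- or two-sided.

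The Synopsis evaluation scheme has patients assessed "at the time of admission, and at 24 and 48 hours in relation to clinical and laboratory aspects". Section 12.1.1 places the clinical form, the signs and symptoms and the blood collection ahead of the Day 1 laser application in both arms. The Day 1 form (Attachment B) has fields for limb circumference on both sides, extent of edema, pain from 0 to 10, and temperature of the affected and contralateral areas. Section 9.2 measures CK from first contact, and the laboratory sheet (Attachment C) has a D1 column.

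Disability appears only in the statistical text. That text gives it a second test: "The Kruskal-Wallis rank sum test was used to compare the disability scores between groups".

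The size is "60 patients, 30 in the treatment group and 30 in the control group".

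**The concern.** For five of the six measures the trial holds a pre-treatment value of the outcome itself, and the 48-hour comparison does not use it. Section 7.2 admits patients at any time within 24 hours of the bite, and Section 8.3 grades local findings from light to severe, so patients may differ widely at entry. No stratification by severity is described, which leaves the analysis as the only stated place to deal with such differences. In a trial of 60, lost precision matters, and a baseline difference that arises by chance carries into the 48-hour difference in proportion to the correlation between the two time points.

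Two smaller matters sit in the same paragraph. If CK is right-skewed, a t-test on raw means is dominated by a few high values. And two tests for disability, with no rule for which one governs, let the better p-value be chosen after the fact.

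**Working it through.** **Inputs from the protocol.** 30 per arm; significance level 0.05 (two-sided assumed); independent-samples t-test at 48 hours; admission values as listed above.

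**Inputs not in the protocol, so assumed over a range.** Standardised effect d = 0.6; baseline-to-48-hour correlation ρ = 0 to 0.7; SD of log CK 0.5 to 1.2 with log-normal CK.

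**The planned size.** The Synopsis offers "60 patients in order to evaluate the effectiveness and safety of low-intensity laser" with no effect size, SD or power, so 60 cannot be reproduced. Back-solving n = 2(1.960 + 0.842)²/d² for n = 30 gives d ≈ 0.72 at 80% power with the unadjusted test.

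**Baseline adjustment.** ANCOVA multiplies the residual variance by 1 − ρ², so the effective standardised effect is d/√(1 − ρ²). The noncentrality is that value times √(30/2), with 58 df for the t-test and 57 df for ANCOVA.

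| Analysis | 1 − ρ² | Effective d | Power | 60 patients act like |
|---|---|---|---|---|
| t-test | – | 0.600 | 63% | 60 |
| ANCOVA, ρ = 0.3 | 0.91 | 0.629 | 67% | 60/0.91 = 66 |
| ANCOVA, ρ = 0.5 | 0.75 | 0.693 | 75% | 60/0.75 = 80 |
| ANCOVA, ρ = 0.7 | 0.51 | 0.840 | 89% | 60/0.51 = 118 |

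A further allowance for chance imbalance in the covariate (standard error inflated by √(1 + 1/56)) lowers each ANCOVA figure by less than 1 point, to 66%, 74% and 89%. At ρ = 0 it gives 62.0% against 62.8% for the t-test. That is the cost of adjusting for a useless covariate.

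**Chance imbalance.** The standard error of a baseline mean difference, in SD units, is √(2/30) = 0.258. A difference of at least 0.25 SD in either direction therefore has probability 2 × P(Z > 0.25/0.258) = 0.33, about one trial in three.

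**CK, raw against log scale.** Simulation with log-normal data, 30 per arm, 20,000 runs, a true halving (a shift of ln 2 = 0.693 on the log scale) and no baseline adjustment:

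| SD of log CK | Raw t-test | Log t-test |
|---|---|---|
| 0.5 | over 99% | over 99% |
| 0.8 | about 80% | 91% |
| 1.0 | 57% | 75% |
| 1.2 | 37% | 59% |

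With no true difference, the raw t-test rejects in about 4% to 5% of runs across these SDs, so it is slightly conservative and not inflated.

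**Disability.** Under the null with normal data, each test alone rejects in about 5% of runs. Counting a result when either test has p < 0.05 gives about 6.0%.

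**The case against.** The strongest reply is that nothing here is invalid. Under randomisation the unadjusted t-test is unbiased, and chance imbalance is already reflected in its standard error. That stands. A reader might infer that the 48-hour result would be biased, or its error rate inflated; neither follows. The loss is of efficiency, together with an estimate that can be shifted by imbalance in the one trial that is run.

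The gain is also conditional. The protocol gives no correlation and has features that could lower it: Section 4.1 describes local effects as progressive, patients enter at different points of that course, and the Day 1 form rates pain after analgesia. At ρ = 0.3 the gain is only about 4 points. This limits the size of the gain but not the advice, since the loss at zero correlation is under 1 point.

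Three further readings go beyond the documents. It is tempting to say that every measure is taken at admission, but the text shown has no instrument, schedule or Day 1 field for disability. It is tempting to call CK skewed as a matter of fact, but no section gives its distribution. And the change is not wholly free: logging CK replaces a difference in means by a ratio of geometric means.

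Finally, baseline is not entirely unused. The log-rank analysis of time to a 50% reduction is relative to each patient's earlier value. It is a separate analysis, however, and does nothing for the 48-hour t-tests.

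**Conclusion.** The point holds for five measures: CK, pain, circumference ratio, edema extent and temperature difference. Section 13.2 itself fixes an unadjusted test, so this is a stated choice and not a detail left to an analysis plan. At an assumed effect of 0.6 SD, adjustment adds about 4, 12 and 26 points of power at correlations of 0.3, 0.5 and 0.7, against a loss of under 1 point at zero. The direction is secure; the size rests on a correlation that the protocol does not give.

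The case for logging CK depends on right skew. For a true halving the gain runs from nothing of note at a log-SD of 0.5 to about 22 points at 1.2.

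The double test of disability is real but separate and small, at about 6% instead of 5%.

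This is a change that should be made, not a defect that invalidates the trial.

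**What to change.** - For the five measures, make the main 48-hour comparison an ANCOVA of the 48-hour value on arm and the admission value of the same measure. Hours from bite to admission may be added; Attachment A already records the times needed. Keep the t-test as a sensitivity analysis.
- Prespecify CK on the log scale at both times and report a geometric mean ratio with its confidence interval. State that this presumes right skew and that the estimand is a ratio.
- Name one test for disability as the one that counts. Do not add baseline adjustment there unless an admission assessment exists.
- Make the same changes in the Synopsis, which repeats the text of Section 13.2.

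The cost is wording. No extra patients, visits or measurements are needed for the five measures. The statistical price is one degree of freedom per model (two if time from bite is added) and the change of estimand for CK.
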